### Secondary efficacy endpoints

(1) Changes in atrial fibrillation load at 3 months, 6 months, and 1 year after treatment. Atrial fibrillation load was defined as the longest duration of atrial fibrillation episodes, the number of episodes of atrial fibrillation, and the percentage of time patients were in atrial fibrillation during a given monitoring period.

(2) Time of first occurrence of atrial flutter/atrial fibrillation.

(3) Incidence of electrical cardioversion within 1 year after treatment.

(4) Changes of transthoracic echocardiographic indexes at 1 year after treatment.

(5) Incidence of stroke and thromboembolism at 6 months and 1 year after treatment.

(6) Health Survey Summary Form (SF-36) score within 1 year after treatment.

Safety endpoints

(1) Adverse events (AEs): Any adverse medical events occurring between the time subjects signed the informed consent and were enrolled in the study and the last follow -up, regardless of whether there was a causal relationship with the study drug, was considered an adverse event. The sum of "definitely relevant", "possibly relevant" and "unascertainable" associated with the study drug was the adverse reactions (ADRs) of the study drug, and the incidence of adverse reaction was calculated accordingly.

(2) Laboratory indicators: blood routine, urine routine, stool routine, biochemical examination and coagulation function examination;

(3) Clinical physical examination and vitals.

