# Statistical analysis Methods

General principles of statistical analysis

Statisticians are responsible for developing a statistical analysis plan (SAP) with the principal investigator after the protocol is confirmed. Statistical analysis will be performed with SAS 9.4 (or higher version; SAS Institute, Cary, NC). The sample size is calculated using PASS13 software (NCSS, Kaysville, UT).

A 2-tailed P<0.05 will be considered statistically significant in all statistical tests. (If no other specification). No adjustments for multiple comparisons were made.

Qualitative data will be described with frequencies and percentages; quantitative data will be described with mean and standard error or with median and interquartile interval, minimum and maximum.

Continuous variables will be summarized with mean and SD and compared using paired t-test or Wilcoxon rank test, as appropriate. Categorical variables will be summarized with frequencies and percentages and compared using chi-square test or Fisher exact test, as appropriate. Ranked variables will be compared using Wilcoxon rank test or CMH test.

Enrolment Analysis

Enrollment analysis will summarize the number of enrollment and the number of subjects who completed the trial of each site and lists dropout subjects.

The dataset size between groups, subjects' disposition between sites, dropout rate and termination reasons will be listed in detail

Baseline and demographic characteristics

Baseline characteristics of patients will be described overall and per group.

Demographic and baseline characteristics (age, gender, height, BMI, vital signs, etc.), medical history, family history of atrial fibrillation, drug allergy, etc. of the subjects will be summarized. T-test or Wilcoxon rank-sum test will be used in baseline comparison of continuous variables such as age, height, and BMI between the two groups. The chi-square test or Fisher’s exact test will be used in the baseline comparison of categorical variables such as gender, and medical history

Analysis of efficacy

Both mITT and PPS were used for effectiveness analysis. Analysis performed on PP populations using the same methods can be considered as a sensitivity analysis.

(1) Baseline: The baseline of each relevant efficacy endpoints was described. For comparison methods between groups, refer to the general statistical method above.

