Aimed at changes in atrial fibrillation load at 3 months, 6 months and 1 year after treatment, the mean, standard deviation, median, minimum, maximum, lower quartile (Q1) and upper quartile (Q3) of atrial fibrillation load at each visit site were calculated according to the form of quantitative endpoints. T-test or Wilcoxon rank sum test were used to compare it between the two groups. At the same time, the changes of atrial fibrillation load compared with baseline at 3 months, 6 months and 1 year after treatment were statistically described, and T-test or Wilcoxon rank sum test was used to compare the changes between the two groups.

The time of the first occurrence of atrial fibrillation/atrial fibrillation was analysed as the secondary endpoint. The occurrence days of atrial fibrillation/atrial fibrillation were calculated by the date of radiofrequency ablation surgery as the starting date, the occurrence days= the date of the first occurrence of atrial fibrillation/atrial fibrillation-the date of radiofrequency ablation surgery +1. For patients with atrial flutter/atrial fibrillation, the mean, standard deviation, median, minimum, maximum, lower quartile (Q1) and upper quartile (Q3) of occurrence time were calculated according to the form of quantitative variables. T-test or Wilcoxon rank sum test were used to compare the occurrence time between the two groups.

The secondary efficacy endpoint of transthoracic echocardiography one year after treatment were analysed. The indexes of transthoracic echocardiography mainly included left ventricular end-diastolic volume, left ventricular end-systolic volume, ejection fraction, stroke volume, cardiac output and other evaluation indexes. The mean, standard deviation, median, minimum, maximum, lower quartile (Q1) and upper quartile (Q3) of the results of the evaluation indicators were calculated according to the form of quantitative variables, and T-test or Wilcoxon rank sum test were used to compare the evaluation variables between the two groups.

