The incidence of cardiac cardioversion within 1 year after treatment and the incidence of stroke and thromboembolism at 6 months and 1 year after treatment were analysed as secondary efficacy endpoints. The incidence and incidence difference of the two groups in the experimental group and the control group were described according to general principles. Meanwhile, Chi-square test or Fisher exact probability method were used to compare the incidence between the two groups.

SF-36 score within 1 year after treatment were analysed, and the mean, standard deviation, median, minimum, maximum, lower quartile (Q1) and upper quartile (Q3) of each dimension score were calculated according to the form of quantitative endpoints. And T-test or Wilcoxon rank sum test were used to compare the scores of each dimension between the two groups. It includes 8 dimensions and an overall score. The score of each dimension is calculated as follows:

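### The echocardiographic endpoint is defined as a change at 1 year, but only the one-year values are compared and the baseline is left unused

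*SAP*

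**What the plan says.** **Echo, definition.** SAP section 3.1.2, item (4): "Changes of transthoracic echocardiographic indexes at 1 year after treatment".

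**Echo, analysis.** Section 6.4 (3) opens with "The secondary efficacy endpoint of transthoracic echocardiography one year after treatment were analysed". It lists the indexes, asks for summary statistics of their results, and ends with "T-test or Wilcoxon rank sum test were used to compare the evaluation variables between the two groups". Neither baseline nor change is mentioned, and no treatment difference or confidence interval is requested.

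**AF load, for contrast.** In the same part of section 6.4, AF load is first compared between groups by its values. A second step then describes change from baseline, and "T-test or Wilcoxon rank sum test was used to compare the changes between the two groups".

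**SF-36.** Section 3.1.2, item (6), defines the endpoint as "Health Survey Summary Form (SF-36) score within 1 year after treatment". Section 6.4 says "T-test or Wilcoxon rank sum test were used to compare the scores of each dimension between the two groups".

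**Baselines.** Section 6.4 (1) says "The baseline of each relevant efficacy endpoints was described" and refers the between-group comparison of those baselines to the general rule in section 6.1. Under that rule continuous variables are "compared using paired t-test or Wilcoxon rank test, as appropriate".

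**The concern.** An analyst who follows section 6.4 literally will report one-year echo values under an endpoint called change. The AF load paragraph shows that the authors wrote out a change analysis where they wanted one, so the echo paragraph cannot safely be read as shorthand for the same thing. If the choice stays open, it could be settled after results by treatment code are visible.

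The second issue is efficiency. Defining the echo endpoint as a change presupposes a baseline value. Leaving that value out of the comparison gives a wider interval than the same data could support whenever baseline and 1-year values are correlated.

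A smaller point lies in section 6.1. The only t-test named there is the paired one, and the between-group comparison of baseline efficacy values is sent to that rule. A paired t-test cannot be applied to two independent randomised arms.

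**Working it through.** **Inputs.** Section 2.5 gives recurrence of 39.8% against 30%, 368 evaluable patients per arm, 80% power, 5% significance and 20% loss. Section 6.1 gives two-sided testing. The correlation *r* between baseline and 1-year echo values is not in the SAP. I assume 0.3, 0.5 and 0.7.

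**The plan's own figure.** With unpooled variance, n per arm = (1.960 + 0.842)² × (0.398×0.602 + 0.30×0.70) / 0.098² = 367.4, so 368. Then 368/0.80 = 460 per arm and 920 in total. The figures reproduce. They concern AF recurrence only; the SAP states no power for echo or SF-36. I use 368 per arm below simply as a plausible number with 1-year data.

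**Variance of the treatment difference**, relative to comparing 1-year values, in large samples, with equal SDs at both times and a common slope in the two arms:

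- 1-year values alone: 1
- change scores: 2(1 − r)
- 1-year value adjusted for baseline (ANCOVA): 1 − r²

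Since 2(1 − r) − (1 − r²) = (1 − r)² ≥ 0, ANCOVA is never less precise than change scores. Since r² ≥ 0, it is never less precise than the 1-year values alone.

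**Power.** With 368 per arm, the unadjusted comparison has 80% power for a difference of 2.802 × √(2/368) = 0.207 SD. For that same difference, power is Φ(2.802/√V − 1.960), where V is the relative variance.

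| r | V, change score | Power, change score | V, ANCOVA | Variance reduction, ANCOVA | Power, ANCOVA | Equivalent extra patients, 1/V − 1 | Adjusted n per arm matching 368 unadjusted |
|---|---|---|---|---|---|---|---|
| 0.3 | 1.40 | 65.8% | 0.91 | 9% | 83.6% | 10% | 335 |
| 0.5 | 1.00 | 80.0% | 0.75 | 25% | 89.9% | 33% | 276 |
| 0.7 | 0.60 | 95.1% | 0.51 | 49% | 97.5% | 96% | 188 |

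A change-score t-test would cure the mismatch but loses precision when r is below 0.5.

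**Why ANCOVA also answers the change question.** If Y₁ = a + bT + cY₀, then Y₁ − Y₀ = a + bT + (c − 1)Y₀. The treatment coefficient b is the same for the 1-year value and for the change, so one model serves the endpoint as named.

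**The case against.** The case against has real weight.

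- **No bias as such.** Under randomisation with complete data, the difference in 1-year means is unbiased for the difference in mean change, and chance baseline imbalance is already reflected in the standard error. This stands. It does not cover missing data: section 2.5 allows 20% loss and section 5 rules out imputation for secondary endpoints.
- **No design target is missed.** The sample size rests on recurrence alone, so the loss of precision breaks no stated power claim. This stands.
- **The gain depends on r.** At r = 0.3 power rises only from 80% to 83.6%. This stands, and is why the low end is shown.
- **The echo paragraph may point back to endpoint (4).** It speaks of the secondary echo endpoint, which might be taken to mean the change. The reading is weak, because what it summarises and tests are results one year after treatment.

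A reader might also infer three stronger points, which the SAP does not support.

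- *That SF-36 has the same mismatch.* It is defined as a score and analysed as a score.
- *That baselines are shown to exist for every efficacy endpoint.* Section 6.4 (1) speaks of each relevant endpoint and names no SF-36 baseline. An echo baseline follows from the word *changes*; an SF-36 baseline is only a possibility.
- *That treatment effects would be tested by a paired t-test, or by t-tests alone.* Section 6.4 names its own tests for these endpoints and allows the Wilcoxon rank sum test. The demographic comparison in section 6.3 does the same. The paired wording reaches only the between-group comparison of baseline efficacy values.

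**Conclusion.** The point holds for echocardiography. Sections 3.1.2 and 6.4 disagree on whether the endpoint is a change or a one-year value, and this conclusion needs no assumption. The accompanying loss of precision is 9% to 49% of the variance for r from 0.3 to 0.7, an assumed range that also rests on the large-sample formulae above. For SF-36 there is no contradiction, only an optional gain in efficiency if a baseline was collected. The paired-test wording in section 6.1 is a minor separate error with no bearing on any treatment-effect test. All of this concerns secondary endpoints and baseline description, so the conclusion on AF recurrence does not change. It should be corrected, but it is not critical.

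**What to change.** 1. **Echo (section 6.4).** For each index, fit a linear model of the 1-year value on treatment and its own baseline value. Report the adjusted difference with 95% CI. Keep the rank-based test as a supportive analysis for clearly non-normal indexes.
2. **SF-36 (section 6.4).** State which visit is analysed, since the definition covers a period of up to 1 year. If a baseline was collected, use the same model for the dimension scores. Keep the Wilcoxon test for coarse scales: by Table 1 the raw scores of RP and RE span only 4 and 3 points.
3. **Missing baselines (section 5).** Add a simple rule. Without one, patients who have a 1-year value but no baseline drop out of the model.
4. **General rule (section 6.1).** Name the two-sample t-test for between-group comparisons and keep the paired t-test for within-group change.

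The cost is SAP wording and a little more code, with no new data. The one small downside is the handling of missing baselines, which item 3 covers. The change should be made before database lock and the first unblinding. If it is made later, it should be documented in the analysis report, as section 1 requires for modifications.

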## Sample Size

Referred to《Catheter ablation vs. antiarrhythmic drug treatment of persistent atrial fibrillation: a multicentre, randomized, controlled trial (SARA study)》(European Heart Journal, 2014 Volume 35, Issue 8, Pages 501-507).

Assumed the 1-year recurrence rate of patients with persistent AF after radiofrequency ablation is 39.8% (the duration of an episode of AF/flutter/atrial tachycardia recorded by ECG≥30s 3 months after ablation is considered as a recurrence of AF). We predicted that the 1-year recurrence rate of atrial fibrillation could be reduced to 30% by adding Shensong Yangxin capsule after radiofrequency ablation. Therefore, we may expect that sample size of minimum 368 patients in each study group will provide the study with 80% power to detect a difference in primary outcome at 5% of significance. Accounting for 20% of lost to follow up patients of the trial, we need to include 460 patients in each group and the total sample size is 920.

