# Selection of populations

All analyses were performed on patients undergoing radiofrequency ablation and will not include patients who were followed for less than 3 months and did not complete the blanking period.

The primary analysis will be for a modified intent to treat population set (mITT), which included all randomized patient with the exclusion of patients that did not provided consent, failure to receive treatment or without any valid data collected after randomization. Following the intention-to-treat principle, patients will be analysed according to the procedure assigned.

Per-Protocol set (PPS) population: a subset of the mITT analysis set, including all patients randomized, treated without major protocol violations/deviation.

pre-defined major protocol violations/deviations are:

- poor compliance in treatment, that is, less than 80% adherence to taking the drug;
- missing data for the primary efficacy endpoint
- major violation of the research protocol, such as non-respect of the randomized procedure allocation and/or duration (wrong procedure followed, premature discontinuation of procedure)

Not pre-defined major protocol deviations identified during a blinded data review before final database lock will be classified.

Safety set (SS): All patients who received at least one treatment after randomization. Patients will be analysed according to procedure received

Measures of efficacy were analysed using mITT and PPS populations, respectively. Safety was analysed by SS population.

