# Processing of missing data

In this study, survival analysis was used to analyse the 1-year recurrence of atrial fibrillation for the primary efficacy endpoint. mITT and PPS were both included for the patients who failed to complete the 1-year follow-up due to half-way drop out or missing follow-up. The endpoint was defined as censored in the statistical analysis, and the censored date was the last follow-up date. No carry-over of missing data or multiple fillings of missing data were performed.

Missing data of secondary endpoints and safety endpoints, no filling or other processing is carried out.

Handling of dates: When only part of the date is known, the following rules are used to calculate the duration. If the start time (such as the date of first onset of AF or the date of diagnosis) is partially missing and only the day is missing, then fill in the first day of the corresponding month. If the end date is partially missing and only the day is missing, replace it with the last day of the month. If both the day and month of the date are missing, this date is treated as missing.

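### Cardioversion and stroke/thromboembolism are tested on crude incidence with no rule for patients lost after month 3, whom the same SAP censors for the primary endpoint

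*SAP*

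**What the plan says.** SAP section 3.1.2 defines two secondary endpoints as events over a fixed period: "Incidence of electrical cardioversion within 1 year after treatment" and "Incidence of stroke and thromboembolism at 6 months and 1 year after treatment". Section 6.4 describes each arm's incidence and the difference between arms, and then: "Chi-square test or Fisher exact probability method were used to compare the incidence between the two groups". It does not mention time at risk, censoring or who belongs in the denominator.

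Three other sections bear on this:

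- **Section 2.5** inflates the sample size: "Accounting for 20% of lost to follow up patients of the trial".
- **Section 4** says of all analyses that they "will not include patients who were followed for less than 3 months and did not complete the blanking period", and that "Measures of efficacy were analysed using mITT and PPS populations, respectively". Patients lost between month 3 and 1 year therefore stay in.
- **Section 5** confirms that both sets include patients who did not complete the year. For the primary endpoint it gives a rule: "The endpoint was defined as censored in the statistical analysis, and the censored date was the last follow-up date". For the secondary endpoints it gives none: "Missing data of secondary endpoints and safety endpoints, no filling or other processing is carried out".

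**The concern.** A patient lost at month 7 without a stroke has an unknown 1-year status. A two-by-two table cannot show that. The analyst must count the patient as event-free, drop the patient only if no event was seen before loss, or drop every lost patient together with any observed events. The first two give different incidences from the same data. The third discards follow-up that was collected. The SAP does not choose among them, so the choice could be made after the data are seen.

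For the same patients over the same year, the SAP handles incomplete follow-up of the primary endpoint by censoring, Kaplan-Meier, log-rank and Cox. These two endpoints are also datable events, but they do not get that treatment. At stake are the reported incidences and their difference and, if loss differs between arms, the comparison itself.

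**Working it through.** **The plan's own figure.** Two proportions, 39.8% vs 30%, two-sided 5%, 80% power, unpooled variance: n = (1.960 + 0.842)² × (0.398×0.602 + 0.30×0.70) / 0.098² = 7.849 × 0.4496 / 0.009604 = 367.4, so 368 per group. With 20% loss, 368 / 0.80 = 460. Both figures reproduce. The allowance equals 0.20 × 460 = 92 patients per group.

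**Assumptions.** The SAP gives no cardioversion or stroke rate, so a true 1-year risk of 10% is assumed, with a range of 2% to 15%. Event and loss hazards are constant and independent of each other. Loss reaches 20% by 1 year, starting either at day 0 or, because section 4 removes earlier losses, only after month 3.

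**Equal 20% loss after month 3, true risk 10%.**

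- Event hazard λ = −ln(0.90) = 0.1054 per year.
- Loss hazard after month 3: μ = −ln(0.80) / 0.75 = 0.2975 per year.
- Events by month 3: 1 − exp(−0.1054×0.25) = 0.0260.
- Events observed later: 0.9740 × [0.1054 / 0.4029] × [1 − exp(−0.4029×0.75)] = 0.0664.
- (A) All patients in the denominator: 0.0260 + 0.0664 = **9.2%**.
- (B) Patients lost without an event removed, earlier events kept. Event-free completers are 0.90 × 0.80 = 0.72, so 0.0924 / (0.0924 + 0.72) = **11.4%**.

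A linear check of (A): three quarters of events fall after month 3, when on average half of the loss has occurred. That gives 10% × (1 − 0.375×0.20) = 9.25%.

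| Loss begins | (A) counted event-free | (B) lost without event removed |
|---|---|---|
| Day 0 | 9.0% | 11.1% |
| After month 3 | 9.2% | 11.4% |

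Across true risks of 2% to 15%, (A) gives 0.90 to 0.92 times the true risk and (B) gives 1.10 to 1.15 times. Kaplan-Meier would recover the true risk under the same independence assumption.

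**Effect on the comparison.** With equal loss, a true 6% vs 10% (risk ratio 0.600) is seen under (A) as a risk ratio of 0.599 to 0.600. The risk difference shrinks from 4.0 points to 3.6 or 3.7. Type I error stays at 5%.

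With unequal loss and no true effect, the risk ratio (arm with more loss over arm with less) at a true risk of 10% is:

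| Loss | Begins | (A) | (B) |
|---|---|---|---|
| 15% vs 25% | Day 0 | 8.71/9.24 = 0.94 | 11.43/10.78 = 1.06 |
| 15% vs 25% | After month 3 | 9.04/9.44 = 0.96 | 11.81/10.98 = 1.08 |

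At 10% vs 30% loss, over true risks of 2% to 15%, the ranges are 0.89 to 0.92 and 1.12 to 1.17. The approximate type I error of the 5% test at 10% risk is 5.5% to 6.5% for 15% vs 25%, and 7.0% to 11.0% for 10% vs 30%. These use 460 per group for (A) and 368 for (B).

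**The case against.** A reader might infer that the incidences are biased low and that the arm losing more patients will look better. The SAP does not support this. It holds only if lost patients count as event-free. If patients lost without an event leave the denominator, which the no-processing rule can also mean, the bias is upward and the arm with more loss looks worse. If every lost patient is removed with all events, and loss is independent of events, there is no bias, only lost information.

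A reader might also place the loss at the start of the year, giving 10% × 0.80 = 8.0%, or 7.5% vs 8.5% at 25% vs 15% loss. Section 4 takes those patients out of every analysis, so these figures do not apply.

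Several further points count against the concern. The 20% is a planning allowance, and what remains after early losses are removed may be smaller. Nothing in a double-blind, placebo-controlled design predicts unequal loss. Proportions at fixed times are a common choice for secondary endpoints. Kaplan-Meier is itself valid only if censoring is non-informative, so it does not cure loss related to outcome. All of this stands and limits the size of the problem. It does not supply the missing denominator rule, nor explain why these endpoints are treated differently from the primary.

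**Conclusion.** The point holds in this form: the SAP fixes a test on crude incidence for two datable events, keeps patients with incomplete follow-up, and does not say how they are counted. The direction of the distortion is undefined. At a true risk of 10% and 20% loss after month 3, the unstated denominator alone moves the reported incidence between about 9.2% and 11.4%. The arm comparison is little affected unless loss differs between arms, and at 15% vs 25% the effect is modest. At lower event rates, as may apply to stroke, the absolute shift is smaller.

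The event rates, the loss patterns and the independence of loss from events are assumptions, not SAP figures. These are secondary endpoints, and the primary analysis is unaffected. The change is worth making because it is cheap and the method is already in the plan.

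**What to change.** In section 6.4, replace the crude comparison for these two endpoints. Estimate the incidence of first cardioversion at 1 year, and of first stroke/thromboembolism at 6 months and 1 year, by Kaplan-Meier, censoring at last contact. Report the difference at each time with a 95% CI and compare arms by log-rank. State the time origin: these endpoints run from treatment, whereas the primary endpoint's clock starts 90 days after ablation and cannot be reused unchanged.

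Keep the crude counts with Fisher's exact test as a prespecified supportive analysis with its denominator written down, so that the choice of test does not depend on the number of events seen. Amend section 5 so that its rule for missing secondary data no longer covers these two endpoints.

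The cost is a few lines of SAP text and reuse of the planned survival code. There are two downsides. With few strokes the Kaplan-Meier difference will be imprecise. The method also assumes non-informative censoring, as the primary analysis already does.
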